**10. ANALYSIS OF RESULTS**

Even though this is a single cohort observational study (SCOS), we will demonstrate power considerations involving a historic control (HC) group - as if it was a randomized study.

The primary end-points ‘Incidence of rejection’ and ‘Rate of surgical complications’ are both categorical parameters and can be treated similarly in power calculations.

**10.1** **Strategy regarding 0-hypothesis**

Regarding the ‘*Incidence of rejection*’, a non-inferior approach seems reasonable. The most important aspect is to avoid the following (Type 1) error: Not detecting an elevated rejection rate in the single cohort observational study group (SCOS), when there in fact is a difference in favor of the historic, control (HC) group, with high-CS dosing.

One could argue to use a one-sided test/“rejection region”, because it is highly unlikely that the low-immunosuppressive regimen will yield a lower incidence of rejection. However, according to statistical tradition, a two-sided test will be demonstrated.

Thus, the *0-hypothesis* will have to be:

H0: *The SCOS group will have a significantly different rejection rate compared to the HC group* (*SCOS Gr.* ≠ *HC Gr.*)

- Between groups comparison of total biopsy-proven rejection rate; based on scheduled and ‘ad hoc’ biopsies from the duodenal segment, pancreas and kidney.

-- Biopsy-proven rejection in either organ (for SPK) contributes to the rejection incidence.

Regarding the ‘*Rate of surgical complications*’, the most important aspect is to avoid the following (Type 1) error: Demonstrating an elevated complication rate in the HC group, when there in fact is no difference.

Also here, one could argue to use a one-sided test/“rejection region”, because it is no reason to believe that the low-immunosuppressive regimen will yield a higher rate of complications. However, according to custom, a two-sided test will be demonstrated. Thus, a natural *0-hypothesis* will be:

H0: *The SCOS group and the HC group will have similar rates of surgical complications* (*SCOS Gr. = HC Gr.*)

- Between groups comparison of surgical complication rate; defined as the fraction of patients experiencing one or more surgical complications, involving reoperation or reintervention.

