**2.1** **Primary objectives**

- Compare the incidence of *acute rejection episodes* at 6, 12, 36 and 60 months after pancreas transplantation, between our single prospective cohort with lower CS vs a historic, retrospective control group (PTx performed during 2011-2013). The incidence of rejection is defined as the fraction of patients in which rejections episodes (one or more) have been proven by biopsies. For SPK rejection in eitherorgan, pancreas or kidney, counts.
- Compare the incidence of *surgical complications*, involving reoperations and reinterventions, between the prospective study group and retrospective control group.

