**10.2 Sample size and Power calculation**

These statistical deductions are based on the ***binomial*** distribution/response and a two-sided test (30, 31):

Pn (1-Pn) + Ps (1-Ps) x c

N patients required per arm: (Pn – Ps)2

Pn: Reference probability; Ps: Probability to be detected; c: Test constant

The assumed reference rates (Pn) for the primary end-points (both actually about 30%) are based on recent data from Norway (12).

By convential presumptions; Power 1-β = 80% ( c = 7,9), and 33% relative change in rejection/complication rates to be detected, these will be the figures:

| End-point | **Rejections** | **Surgical complications** |
| --- | --- | --- |
| Null hypothesis to be tested | H0: SCOS Gr.≠ HC Gr.  H1: SCOS Gr. = HC Gr. | H0: SCOS Gr. = HC Gr.  H1: SCOS Gr. ≠ HC Gr. |
| Statistical model | Binomial distribution; two-sided test | |
| Assumed reference rate (Pn) | 0.30 | 0.30 |
| Effect to be detected (Ps) | ≥ 0.40 (≥ 33% increase) | ≤ 0.20 (≤ 33% decrease) |
| Type I error (α) | 5% | |
| Power (1-β)  c | 80%  7,9 | |
| Number of pats required | 355 per arm | 292 per arm |

If we significantly release on the statistical presuppositions/demands - by only claiming 60% Power ( c = 5,4) and 100% relative change in detected rejection/complication rates - these will be the figures:

| End-point | **Rejections** | **Surgical complications** |
| --- | --- | --- |
| Null hypothesis to be tested | H0: SCOS Gr.≠ HC Gr.  H1: SCOS Gr. = HC Gr. | H0: SCOS Gr. = HC Gr.  H1: SCOS Gr. ≠ HC Gr. |
| Statistical model | Binomial distribution; two-sided test | |
| Assumed reference rate (Pn) | 0.30 | 0.30 |
| Effect to be detected (Ps) | ≥ 0.60 (≥ 100% increase) | ≤ 0.15 (≤ 100% decrease) |
| Type I error (α) | 5% | |
| Power (1-β)  c | 60%  5.3 | |
| Number of pats required | 27 per arm | 80 per arm |

*Practicability with regard to statistics:*

1. It is totally unrealistic – for any Tx-center in the world – to include 600-700 PTx patients, during any reasonable time frame. In Oslo, we are by far the highest volume center in Scandinavia. Our 28 PTx’s performed in 2012 represent 5.6 p.m.p. (per million population), which actually is far higher than any other country in the world, according to figures presented by the Council of Europe in cooperation with the Spanish Tx organization (32). Even if we cooperated/coincluded with all the other PTx centers in Scandinavia (Uppsala/Göteborg/Helsinki), the potential would not exceed 50 patients annually.

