**10.3 Statistical methods in data analysis**

- The primary evaluation criteria ‘Incidence of rejection’ and ‘Rate of surgical complications’ will be evaluated for several populations:

- All patients who receive at least one dose of study medication, defined as the ‘Intention-to-Treat’ population.

- All patients who complete 12 months of intended study medication, defined as the ‘Intention completed’ population.

The analysis of these categorical parameters will consist of:

1. Comparisons of groups using the Fisher exact test.

2. Confidence intervals of 95% of the percentage of incidence of these

events.

- The loss of grafts and deaths will be analysed by the Kaplan-Meier method for estimating the time to events.
- Continuous (non-categorical) variables will be analyzed by student t-tests and chi-square tests.
- Microdialysis data are typically non-normally distributed. We will therefore use the Wilcoxon Signed rank test for repeated measurements and the Mann-Whitney U test for comparison of groups. We will also use linear mixed model analyses on log10 transformed data for repeated measurements. Receiver operating curves and contingency tables will be used to explore sensitivity and specificity.
- Any other methods that are not planned can be considered as alternative methods.

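### The rejection endpoint is framed as non-inferiority, but the hypotheses have no margin and the Fisher test has the opposite null, so the error that matters most is not held at 5%

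*Protocol*

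**What the plan says.** Section 10.1 says of rejection that "a non-inferior approach seems reasonable". The error it most wants to avoid, labelled Type 1, is "Not detecting an elevated rejection rate in the single cohort observational study group (SCOS") when the historical control group (HC) is truly better. It keeps a two-sided test and writes the null hypothesis as "The SCOS group will have a significantly different rejection rate compared to the HC group".

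The tables in Section 10.2 repeat that null and add "H1: SCOS Gr. = HC Gr", with a Type I error of 5%. The rates 0.40 and 0.60 are labelled as effects to detect: "Effect to be detected (Ps) | ≥ 0.40 (≥ 33% increase") in the upper table and "≥ 0.60 (≥ 100% increase") in the lower. Neither is called a margin, and no margin appears elsewhere.

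Section 10.3 plans "Comparisons of groups using the Fisher exact test" for both primary endpoints, plus 95% confidence intervals for the incidence percentages. It mentions no interval for the difference between groups. Section 2.1 makes rejection a primary comparison "at 6, 12, 36 and 60 months after pancreas transplantation".

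**The concern.** A non-inferiority question needs a null of the form 'worse by at least a stated amount', so that rejecting it supports the claim. Here the null is any difference at all and the alternative is exact equality. Data cannot exclude every non-zero difference, however small, so this null can never be rejected. It also contains the phrase 'significantly different', which describes a test result and not a population rate.

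The Fisher test works the other way round: it can reject equality but cannot establish it. Set against the hypotheses as written, the only result pointing towards the alternative is a non-significant p-value, and that result becomes more likely as the study gets smaller. The conclusion at stake is a primary one: whether the reduced corticosteroid regimen leaves the rejection rate no higher than before.

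**Working it through.** **Inputs.** Control rate 0.30, two-sided alpha 5%, and c = 7.9 (80% power) or 5.4 in the text and 5.3 in the table (60% power), all from Section 10.2. Prospective cohort of 60–80 from Section 5. The control group's size is not stated. Section 2.1 gives its period as 2011–2013, and Section 1.1 gives 22 transplants in 2011 and 28 in 2012. Assuming 25 for 2013 gives 22 + 28 + 25 = 75. Equal groups of 60 and of 80 serve as a range.

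**Step 1: the plan's own sizes.** The formula is N = [Pn(1−Pn) + Ps(1−Ps)] × c / (Pn−Ps)².

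- 0.30 vs 0.40: (0.21 + 0.24) × 7.9 / 0.01 = 355.5 (stated 355).
- 0.30 vs 0.60: (0.21 + 0.24) × 5.4 / 0.09 = 27.0, or 26.5 with c = 5.3 (stated 27).

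Both figures reproduce, but as sizes for detecting a difference. The formula has no margin term.

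**Step 2: which error is which.** The Fisher null is equality, so its 5% limits false claims of a difference. Missing a raised rate means failing to reject equality when it is false. That is a Type II error, equal to 1 − power. The plan itself sets it at 20% in the upper table and 40% in the lower, each for that table's own effect and sample size.

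**Step 3: size of that error.** Exact enumeration over all binomial outcomes, control rate 0.30. The entries are the probability of a non-significant two-sided Fisher test.

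| True study rate | 70 vs 75 controls | 60 vs 60 | 80 vs 80 |
| --- | --- | --- | --- |
| 0.40 | 79.2% | 84.5% | 78.5% |
| 0.45 | 58.1% | 67.6% | 56.4% |
| 0.50 | 33.6% | 45.8% | 32.3% |
| 0.60 | 4.4% | 10.6% | 4.1% |

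For example, 18/60 against 29/60 (30% vs 48%) gives p = 0.061. The difference is 18.3 points, with a simple (Wald) 95% interval of about +1 to +35 points.

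**Step 4: what an interval would show.** With 30% in both groups, the half-width is 1.96 × √(0.21/n₁ + 0.21/n₂):

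- 60 vs 60: 16.4 points
- 70 vs 75: 14.9 points
- 80 vs 80: 14.2 points

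Even identical observed rates would not exclude the 10-point increase used in the upper table.

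**Step 5: feasibility of a margin.** The margins here are assumptions, since the protocol gives none. Both true rates are 0.30, the test is one-sided at 2.5%, and power = Φ(margin/SE − 1.96) with SE = √(2 × 0.21/n).

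| Margin | Power, 60 per group | Power, 80 per group |
| --- | --- | --- |
| 10 points | 22% | 28% |
| 15 points | 43% | 54% |
| 20 points | 67% | 79% |

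The smallest margin with 80% power is about 23 points at 60 per group and 20 points at 80.

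**The case against.** The protocol never says how a non-significant Fisher result will be interpreted. A reader might infer that the plan commits itself to declaring equal rejection; the text does not go that far. Section 10 presents its calculations as power considerations for an observational cohort, and Section 10.2 admits openly that its aims must be modest. This stands, and it makes the misreading a risk and not a rule. It does not make the stated hypotheses testable.

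A reader might also infer from the lower table's 60% power that the study would miss a doubled rate 40% of the time. That is the nominal figure at 27 per arm. At the planned cohort size a doubling is missed about 4% to 11% of the time under the control sizes examined.

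Two other provisions might seem to help. Section 10.3 plans 95% intervals, but of the incidence percentages, with no bound on the difference. Section 10.4 considers stopping if the rejection rate has doubled, at least when 20 patients have reached three months. That check addresses a large early excess and leaves increases of 10 to 20 points untouched.

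Finally, a margin could be left to a statistical analysis plan. But the protocol itself fixes the hypotheses, alpha, sizing formula and test, and these contradict one another.

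**Conclusion.** The point holds for moderate increases in rejection. The hypotheses in Sections 10.1 and 10.2 cannot be tested as written, the sample sizes answer a different question, and the 5% level does not protect against the error the plan ranks first. If the true rate were 10 points above a 30% control rate, the Fisher test would be non-significant in roughly 79% to 85% of trials; at 20 points above, in roughly 32% to 46%. These figures rest on the protocol's 30% reference rate and on assumed control groups of 60 to 80, because the actual number is not stated. The inconsistency itself depends on neither assumption.

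**What to change.** In Sections 10.1 and 10.2, remove the reversed hypotheses and the non-inferiority wording for rejection. In Section 10.3, report the between-group difference in rejection rate with its two-sided 95% confidence interval as the basis for the conclusion. State that a non-significant Fisher test is not evidence of equal rejection. The expected precision, about ±14 to ±16 points, should be stated.

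If the investigators keep a non-inferiority claim, the null should be that the study rate minus the control rate is at least a margin, justified before the control data are compared. Non-inferiority would be claimed only if the upper 95% limit lies below that margin. Step 5 shows that only a wide margin would have reasonable power at this size, so the estimation route is the more realistic one.

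The choice of interval method, and which of the four time points in Section 2.1 takes precedence, are separate matters that this correction does not settle.

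The cost is a change of wording and one extra interval, with no additional patients. The downside is that the permitted conclusion on rejection becomes more modest.

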**10.2 Sample size and Power calculation**

These statistical deductions are based on the ***binomial*** distribution/response and a two-sided test (30, 31):

Pn (1-Pn) + Ps (1-Ps) x c

N patients required per arm: (Pn – Ps)2

Pn: Reference probability; Ps: Probability to be detected; c: Test constant

The assumed reference rates (Pn) for the primary end-points (both actually about 30%) are based on recent data from Norway (12).

By convential presumptions; Power 1-β = 80% ( c = 7,9), and 33% relative change in rejection/complication rates to be detected, these will be the figures:

| End-point | **Rejections** | **Surgical complications** |
| --- | --- | --- |
| Null hypothesis to be tested | H0: SCOS Gr.≠ HC Gr.  H1: SCOS Gr. = HC Gr. | H0: SCOS Gr. = HC Gr.  H1: SCOS Gr. ≠ HC Gr. |
| Statistical model | Binomial distribution; two-sided test | |
| Assumed reference rate (Pn) | 0.30 | 0.30 |
| Effect to be detected (Ps) | ≥ 0.40 (≥ 33% increase) | ≤ 0.20 (≤ 33% decrease) |
| Type I error (α) | 5% | |
| Power (1-β)  c | 80%  7,9 | |
| Number of pats required | 355 per arm | 292 per arm |

If we significantly release on the statistical presuppositions/demands - by only claiming 60% Power ( c = 5,4) and 100% relative change in detected rejection/complication rates - these will be the figures:

| End-point | **Rejections** | **Surgical complications** |
| --- | --- | --- |
| Null hypothesis to be tested | H0: SCOS Gr.≠ HC Gr.  H1: SCOS Gr. = HC Gr. | H0: SCOS Gr. = HC Gr.  H1: SCOS Gr. ≠ HC Gr. |
| Statistical model | Binomial distribution; two-sided test | |
| Assumed reference rate (Pn) | 0.30 | 0.30 |
| Effect to be detected (Ps) | ≥ 0.60 (≥ 100% increase) | ≤ 0.15 (≤ 100% decrease) |
| Type I error (α) | 5% | |
| Power (1-β)  c | 60%  5.3 | |
| Number of pats required | 27 per arm | 80 per arm |

*Practicability with regard to statistics:*

1. It is totally unrealistic – for any Tx-center in the world – to include 600-700 PTx patients, during any reasonable time frame. In Oslo, we are by far the highest volume center in Scandinavia. Our 28 PTx’s performed in 2012 represent 5.6 p.m.p. (per million population), which actually is far higher than any other country in the world, according to figures presented by the Council of Europe in cooperation with the Spanish Tx organization (32). Even if we cooperated/coincluded with all the other PTx centers in Scandinavia (Uppsala/Göteborg/Helsinki), the potential would not exceed 50 patients annually.
2. The maximally realistic number of PTx patients to be included in Oslo during a reasonable time frame (2-3 years) will be 60-80.
3. Thus, our intentions with regard to statistical Power have to be more modest. The above figures (lower table) do however show that a doubled rejection rate in the trial arm can be detected at 60% Power with 27 x 2 = 54 patients.
4. The prospects/visions of this study consist of a lot more than detecting significant changes in rejection/complication rates. Please, cfr. paragraphs 2.2 – 2.6 of this protocol. The simultaneous biopsy strategy (D- + P- + K-biopsies) is unique. And the ‘molecular biology’ analyses of these simultaneous biopsies and blood samples have the potential to provide new insights. Furthermore, “new” potential rejection markers (C-peptide; CRP/Amylase/Lipase combined parameter) will be explored.

**10.3 Statistical methods in data analysis**

- The primary evaluation criteria ‘Incidence of rejection’ and ‘Rate of surgical complications’ will be evaluated for several populations:

- All patients who receive at least one dose of study medication, defined as the ‘Intention-to-Treat’ population.

- All patients who complete 12 months of intended study medication, defined as the ‘Intention completed’ population.

The analysis of these categorical parameters will consist of:

1. Comparisons of groups using the Fisher exact test.

2. Confidence intervals of 95% of the percentage of incidence of these

events.

- The loss of grafts and deaths will be analysed by the Kaplan-Meier method for estimating the time to events.
- Continuous (non-categorical) variables will be analyzed by student t-tests and chi-square tests.
- Microdialysis data are typically non-normally distributed. We will therefore use the Wilcoxon Signed rank test for repeated measurements and the Mann-Whitney U test for comparison of groups. We will also use linear mixed model analyses on log10 transformed data for repeated measurements. Receiver operating curves and contingency tables will be used to explore sensitivity and specificity.
- Any other methods that are not planned can be considered as alternative methods.

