#### 4 DURATION OF STUDY

All consecutive PTx recipients during 2-3 years are planned to be enrolled, with an intented number of 60-80 patients. The study will continue until all patients have completed a minimum of 60 months of follow-up or have discontinued participation in the study.

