**9.4 Follow Up of Adverse Events**

Any abnormal laboratory values, abnormal clinical findings and adverse events which are of clinical significance, in the opinion of the investigator, must be followed with appropriate medical management until resolved.

Individual patients will be excluded from the study if serious adverse effects related to the treatment is observed.

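### Primary rejection is a crude fraction compared by Fisher's test out to 60 months, so study patients who withdraw or are excluded before a proven rejection become non-events in the one-dose population

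*Protocol*

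**What the plan says.** - **Endpoint.** Protocol section 2.1 sets the incidence of rejection, "defined as the fraction of patients in which rejections episodes (one or more) have been proven by biopsies", as a primary outcome. It is compared "at 6, 12, 36 and 60 months after pancreas transplantation" with a retrospective group transplanted in 2011-2013.
- **Analysis.** Section 10.3 gives "Comparisons of groups using the Fisher exact test" and a 95% confidence interval for the percentage. The same section assigns Kaplan-Meier to graft loss and death; rejection is not named there.
- **Populations.** Section 10.3 uses two. The first is "All patients who receive at least one dose of study medication". The second is restricted to patients who completed 12 months of the intended medication.
- **Leaving the study.** Section 9.4 states: "Individual patients will be excluded from the study if serious adverse effects related to the treatment is observed". Section 4 lets the study run "until all patients have completed a minimum of 60 months of follow-up or have discontinued participation in the study". Section 12.2 gives the right to withdraw at any time.
- **Data after leaving.** Section 11.1 asks for whatever data can be retrieved on withdrawn patients. No passage requires rejection follow-up to continue after exclusion or withdrawal.

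**The concern.** A crude fraction is a fair estimate of cumulative rejection only if every patient in the denominator is observed up to the time point. In the one-dose population the denominator is fixed at the first dose and the numerator needs biopsy proof. A patient who leaves early without a proven rejection therefore stays in the denominator and cannot enter the numerator, whatever happens later. The exclusion and withdrawal rules are written for the prospective cohort only.

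The direction matters. Section 10.1 says the error to avoid above all is failing to detect a higher rejection rate in the study cohort. Undercounting rejections in that cohort alone pushes towards exactly that error. The plan already provides a time-to-event method for graft loss and death, but not for this primary endpoint.

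**Working it through.** **1. The plan's own figures.** Section 10.2 uses N per arm = [Pn(1-Pn) + Ps(1-Ps)] x c / (Pn-Ps)^2.
- 0.30 vs 0.40, c = 7.9: (0.21 + 0.24) x 7.9 / 0.01 = 355.5 (stated 355).
- 0.30 vs 0.60, c = 5.4: (0.21 + 0.24) x 5.4 / 0.09 = 27.0 (stated 27).

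Both reproduce. Neither contains an allowance for patients who leave.

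**2. Size of the understatement.** The protocol gives no dropout rate and no timing of rejection, so the following are assumptions:
- True cumulative rejection F of 15, 20, 30, 36 and 40% at 3, 6, 12, 36 and 60 months. Only a reference rate of about 30% comes from section 10.2.
- Loss of r per year, unrelated to rejection, so the share still observed at t months is S(t) = (1-r)^(t/12).
- Optionally, a share e excluded evenly over the first 3 months.

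The expected crude fraction is the sum, over intervals, of the new rejections times the share still observed (taken at mid-interval).

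For r = 3%, e = 0:
- 12 months: 0.15 x 0.9962 + 0.05 x 0.9886 + 0.10 x 0.9774 = 0.2966.
- 60 months: 0.2966 + 0.06 x 0.9409 + 0.04 x 0.8853 = 0.3885.

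For r = 3%, e = 10%, the first term is multiplied by 0.95 and the later ones by 0.90:
- 12 months: 0.1420 + 0.0445 + 0.0880 = 0.2744 (from unrounded terms).
- 60 months: 0.2744 + 0.90 x (0.0565 + 0.0354) = 0.3571.

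| Assumed loss | Crude, 12 mo (true 0.30) | Shortfall, points | Crude, 60 mo (true 0.40) | Shortfall, points |
|---|---|---|---|---|
| 3%/yr | 0.297 | 0.3 | 0.388 | 1.2 |
| 5%/yr | 0.294 | 0.6 | 0.381 | 1.9 |
| 10% early + 3%/yr | 0.274 | 2.6 | 0.357 | 4.3 |
| 10% early + 5%/yr | 0.272 | 2.8 | 0.350 | 5.0 |
| 20% early + 5%/yr | 0.250 | 5.0 | 0.320 | 8.0 |

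If rejections fall earlier within each interval, the first two rows become 0.298/0.391 and 0.297/0.385. That gives the low ends of the ranges: 0.2 points at 12 months and about 1 at 60.

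**3. Does a censoring-aware estimate recover the truth?** In a simulation with true 60-month rejection of 0.30 and 10-30% leaving for reasons unrelated to rejection, the crude fraction ran from 0.297 down to 0.245. One minus Kaplan-Meier stayed at about 0.30. With 50-80% of rejections in the first 6 months, the 6-month gap was at most 0.02.

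**4. Effect on the test.** Let d be the share leaving and u the share of leavers' rejections that occur after leaving. The observed study rate is the true rate x (1 - d x u). For true rates of 0.30 vs 0.60 and 60 per group (control size is not given; equality is assumed), exact Fisher power is:

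| d, u | Observed study rate | Power |
|---|---|---|
| 0 | 0.60 | 89% |
| 10%, 0.5 | 0.57 | 82% |
| 20%, 0.5 | 0.54 | 71% |
| 20%, 1 | 0.48 | 45% |

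The last row is an extreme case.

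**The case against.** **A reader might infer that the protocol classifies leavers as rejection-free.** No sentence says so, and a rule for missing outcomes may sit in an analysis plan that is not shown. This stands as a limit on wording. The result follows from the definition and the denominator when applied as written. It does not apply to rejections proven before leaving, which still count.

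**A reader might also infer that the low-steroid cohort will look better overall.** The documents do not support that. Scheduled biopsies count towards the endpoint (section 10.1), and the study adds percutaneous pancreas biopsies (section 2.3), which could raise the detected rate in the study cohort. Losses among the historical controls are not described; that no exclusion rule is stated for them does not make their follow-up complete. Only the direction of this one mechanism is established.

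**The completer population behaves differently.** Early leavers drop out of both numerator and denominator. Removing early rejecters lowers the fraction, and removing leavers without rejection raises it. If leaving is unrelated to rejection, the fraction is unbiased at 6 and 12 months.

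**Graft loss and death are not part of the problem.** They end observation in both groups. A patient who dies or loses the graft before any rejection contributes none under a competing-risks estimate either. Without withdrawal or exclusion, that estimate equals the crude fraction.

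**The effect may be small.** This is a single national centre giving its routine regimen, and section 11.1 retains retrievable data. Ordinary loss costs at most about 2 points at 60 months. The standard error of a difference at 30% is sqrt(2 x 0.3 x 0.7 / n), about 8 points for n = 60 and 7 for n = 80 per group (equal groups assumed). Nothing in the protocol supports a 10-20% early exclusion rate; it is a what-if. This limits the size, but does not answer why a stated exclusion rule should be allowed to act on one side of a primary comparison.

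**Conclusion.** The concern holds for withdrawal and exclusion in the one-dose population. Followed as written, a study patient who leaves without a proven rejection is in effect a non-event, and the rules that create such patients are stated only for the prospective cohort. Taken alone this lowers that cohort's rejection rate, the direction section 10.1 most wants to guard against. The completer analysis does not repair it, since it substitutes another selection. The net direction of the full comparison remains open.

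The size rests entirely on assumed loss rates and rejection timing. It is about 0.2-0.6 points at 12 months and 1-2 at 60 with loss of 3-5% per year. It is about 2.5-5 and 4-8 points only with 10-20% excluded within 3 months. The point matters chiefly at 36 and 60 months, or if the exclusion rule in section 9.4 is used often. It should be corrected because follow-up lost through exclusion may not be recoverable later.

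**What to change.** 1. State in sections 9.4 and 10.3 that patients who stop the regimen, are excluded or withdraw stay in the one-dose analysis population and, with consent, in outcome follow-up for rejection. This concerns outcome data only, not how such patients are treated.
2. Estimate first biopsy-proven rejection in both groups by cumulative incidence (Aalen-Johansen). Treat death and graft loss as competing events and censor only true loss to follow-up. Report the between-group difference with its 95% confidence interval at 6, 12, 36 and 60 months.
3. Do not treat exclusion for serious adverse effects as non-informative censoring; in immunosuppressed patients it may well be related to rejection risk.
4. Keep Fisher's test as a sensitivity analysis.

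The cost is some extra follow-up and analysis work. It is not a wording change alone: consent must cover follow-up after leaving, and dates of first rejection must be extracted from the historical records.
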